#### Behavioral activation treatment

Behavioral Activation Treatment (BAT) is a structured and validated psychotherapy intervention designed to increase engagement with functional, potentially rewarding behaviors [47]. Treatment proceeds through a series of structured units that (a) provide psychoeducation about depression and alcohol dependence, as well as a rationale for the treatment approach, (b) assess and monitor baseline activity levels, (c) identify and support more functional behaviors and personally valued goals as an alternative strategy to cope with cravings and low mood, (d) monitor, support, and reward achieving behavioral goals, and (e) improve problem solving skills. Previous studies have demonstrated that BAT for depression effectively reduces depressive symptoms and is well tolerated in outpatient settings [48].

#### Mindfulness based therapy

The mindfulness based intervention aims to increase awareness for and help patients to accept situational cues, negative thoughts, feelings, and behavioral impulses that have been associated with drinking [49, 50]. Participants are guided through structured units that (a) provide psychoeducation about depression and alcohol dependence, as well as a rationale for the treatment approach, (b) increase patients’ awareness of different experiences including low mood and cravings, (c) help clients to distance themselves from challenging experiences, e.g. by focusing on their breathing, (d) help them to respond to pleasant and unpleasant sensations with acceptance, and (e) foster their sense of strength and self-efficacy by enduring negative experiences and withstanding behavioral impulses.

### Additional information

The study protocol is in accordance with the Standard Protocol Items: Recommendations for Interventional Trials (SPIRIT) guidelines for reporting interventional trials. Ethical approval and consent has been obtained by the leading ethics committee of the Medical Faculty Mannheim/University of Heidelberg (reference number: 2015-606 N-MA). The study will be conducted in compliance with the guidelines for Good Clinical Practice and the Declaration of Helsinki. Participants will provide informed consent prior to enrolment in the study. The trial is registered in the German Clinical Trial Registration (DRKS00010249). Any changes to the protocol will be described in this trial registry.

The principal investigator (PK), independent from the sponsor and with no competing interests to report, is responsible for data monitoring. All adverse events are documented. Interim analyzes are not planned but cross-sectional comparisons for T1 data will be conducted after inclusion of all T1 participants and before data collections at T2 and FU are completed. The day-to-day management of the study (e.g. contact with the participants and the invitation to conduct online surveys) is carried out by advanced researchers. The publication of the results will be independent of the results of the study, even if the intervention proves to have no influence on brain activation and connectivity. Authorship eligibility will be decided according to the guidelines for safeguarding good scientific practice provided be the German Research Association [51]. A written summary of the results will also be made available to the participants after completion of the study. Data, statistical parameters and statistical code of the study will be made accessible to interested researchers after request. Due to data safety concerns, raw data cannot made openly accessible for the public.

### fMRI assessment battery

#### Reward paradigm

In this event-related paradigm, participants are asked to respond to a flashlight as fast as possible by pressing a button. Preceding the flashlight, an arrow cue informs the participant about the rewarding consequences of their response to the flash stimulus. Four conditions are included in the paradigm: (1) in the so called monetary reward condition (arrow up) participants’ fast response to the flash is rewarded with 2€; (2) in the punishment avoidance condition (arrow down) a slow response is punished by a loss of 2€ while a fast response is rewarded by the avoidance of that loss; (3) the verbal feedback condition (vertical double arrow) allows the participants to receive verbal feedback on their performance; (4) in the passive control condition (horizontal double arrow) no response is required. During the outcome phase, the participants see the reward of the latest trial (“2€”, “0″ or “Fast response!”, “Too slow”) as well as their cumulative total gain at that point in time. In order to ensure that all participants are able to win some money and have comparable winnings, the threshold for a fast response is adaptively tailored for each trial to the individual response times of the subject. The inter-trial interval was randomly varied between 6 and 9 s. Each condition is presented 10 times in a pseudo-randomized trial order with no more than two equal conditions in succession. The total run length is 9 min. The monetary reward anticipation task [52] has been shown to reliably and robustly activate the ventral striatum including the nucleus accumbens [53].

#### Erotic incentive delay task

In order to measure different categories of reward processing, a variant of our own monetary reward task [52] comprising erotic stimuli will be performed. Similar to the description above, participants have to respond to a cued probe to receive either erotic stimuli or matched social control stimuli. Again during the anticipation phase, distinct cues preceding the target inform the participants whether a rewarding erotic image will be shown or not. In previous studies it has been shown that striatal reward-associated brain activations can be reliably observed when erotic pictures are presented [54].

#### Resting state/mood induction paradigm

The so called mood induction paradigm has been successfully implemented in different studies [32]. Here, we will use a modified version of the paradigm in order to directly test intervention associated activation and connectivity patterns. The paradigm consists of five blocks, each of which lasts 4.5 min: a resting state block, a sad mood induction block, one alcohol cue-reactivity block, one mindfulness-based block and one behavioral activation block. The mindfulness-based block and the behavioral activation block are counterbalanced.

During the resting state phase, participants are told to keep their eyes open and background pink noise is presented. During the sad mood induction phase, key words to remind participants of personal negative life events and background sad music (excerpt from Albinoni/Giazotto, Adagio in g-minor) are presented. Participants are asked to concentrate on the negative life events and empathize with the situation. During the alcohol cue-reactivity phase, participants are presented images of either beer or wine (depending on the participants preference) while they receive corresponding audio induction statements instructing them to imagine alcohol-associated situations. In the mindfulness- based phase, again, participants are presented images of beer or wine while this time they listen to mindfulness-based audio instructions. Correspondingly, in the behavioral activation training phase, participants are played audio instructions associated with imagining activities while viewing alcohol-associated pictures. In each phase, 9 alcohol-associated cues are presented for 15 s, while simultaneously 9 audio statements are played. After each picture a fixation cross is presented for also 15 s. After each block, participants are instructed to rate their mood by means of the Positive and Negative Affect Schedule (PANAS), as well as their craving and self-control to abstain. For the T2 assessment, a different set of alcohol-associated pictures is presented.

As mentioned above, the mindfulness-based block and the behavioral activation block are counterbalanced. Thus, a second randomization list will ensure that at T1 the order of the experimental blocks will be equally distributed above all participants. Comorbid patients will receive the reverse order of their T1 assessment at the T2 fMRI scanning.

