### Participants

Sixty comorbid alcohol dependent and depressed patients, 30 alcohol dependent only and 30 depressed only patients will be included for T1 assessment. Further, 30 healthy control participants (matched according to age, gender and educational level) will be recruited.

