### Randomization

After completion of baseline assessment, comorbid patients will be randomly assigned to one of the two group interventions. To reduce the time between the initial study recruitment and the start of the group therapy, the randomization order will be determined with a block randomization with 6 participants per block for each treatment arm. Randomization will be performed by a researcher who is not involved in the recruitment, using a computerized randomization tool implemented in MATLAB (The MathWorks Inc., Natick, Massachusetts, United States). Participants will be recruited and enrolled by trained research staff; the allocation sequence will be concealed from them. Since the study offers psychotherapeutic interventions, patients are not blinded to their intervention arms.

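### Block order is balanced only over the whole sample and reversed at T2, so any position effect adds noise to change in the two therapy-matched blocks unless order is modelled

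*Protocol article*

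**What the plan says.** All of this is in the protocol article, under Methods.

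- **Resting state/mood induction paradigm.** The paradigm has five blocks and was modified "in order to directly test intervention associated activation and connectivity patterns". Two blocks mirror the two therapies, and only these vary in position: "The mindfulness-based block and the behavioral activation block are counterbalanced".
- **Level of balance, same section.** A separate randomised list is meant to see to it that "at T1 the order of the experimental blocks will be equally distributed above all participants". The article names no balance within diagnostic group or therapy arm.
- **Order at T2, same section.** "Comorbid patients will receive the reverse order of their T1 assessment at the T2 fMRI scanning".
- **Participants.** "Sixty comorbid alcohol dependent and depressed patients, 30 alcohol dependent only and 30 depressed only patients will be included for T1 assessment", and "30 healthy control participants (matched according to age, gender and educational level) will be recruited". That makes 150 in total.
- **Randomization.** "After completion of baseline assessment, comorbid patients will be randomly assigned to one of the two group interventions". The T1 block order is thus fixed before the arm is known.
- **Behavioral data analyses.** The planned comparisons are among the four diagnostic groups and between BAT and MBT. Difference scores are to be used, and no order term is named.

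**The concern.** Counterbalancing protects a contrast only at the level at which it is imposed. Here that level is the whole sample, whereas the planned contrasts are between diagnostic groups at T1 and between BAT and MBT over time.

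Reversal at T2 is what makes this matter for change. With the same order at both visits, a constant position effect (fatigue, habituation or carry-over from the preceding block) would subtract out of each patient's change. With reversal it stays in, with a sign that depends on the T1 order. The two blocks affected are those meant to show therapy-related change. At stake is the precision of that comparison, and how easily a single realised result can be read if the arms happen to differ in order mix.

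**Working it through.** The article gives no figure for an order effect, so there is none to reproduce. The inputs are:

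- From Participants: 150 participants, of whom 60 are comorbid, with 30 in each other group. Two arms of 30 are taken for the 60 comorbid patients.
- From Sample size: f = 0.2 for the group x time interaction, and a correlation of 0.7 between repeated measures.
- Assumed: o, the second-minus-first position effect in SD units, is 0.3-0.5. Values of 0.1 and 0.8 are added to show the range.
- Assumed: one unstratified list with 75 participants in each order.

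**1. What reversal does to a change score.** Take one of the two blocks, with true change τ. A patient who has it first at T1 has it second at T2, so the observed change is τ + o. A patient with the opposite order shows τ - o. If a share p of an arm has the first pattern, the arm's mean change is shifted by o(2p - 1), which is zero at p = 0.5. The BAT-MBT difference is shifted by 2o(p_BAT - p_MBT).

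**2. Variance of change.** Without an order effect the variance is 2(1 - 0.7) = 0.60. At an even split, ±o adds o².

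**3. Power for BAT versus MBT.** For the within-between interaction, the noncentrality is λ = N f² × 2/(1 - 0.7). With N = 60 this is 60 × 0.04 × 2/0.3 = 16. Written as a difference δ in mean change, λ = (N/4)δ²/0.60. So δ² = 16 × 4 × 0.60/60 = 0.64 and δ = 0.8 SD. With an order effect, λ = (N/4) × 0.64/(0.60 + o²). The F test has 1 and N - 2 degrees of freedom and α = .05; N = 54 allows for the 10% drop-out in the Sample size section.

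| o (SD) | Variance of change | Increase | Power, N = 60 | Power, N = 54 |
|---|---|---|---|---|
| 0 | 0.60 | - | 97.6% | 96.1% |
| 0.1 | 0.61 | 2% | 97.4% | 95.8% |
| 0.3 | 0.69 | 15% | 95.6% | 93.5% |
| 0.5 | 0.85 | 42% | 91.1% | 87.9% |
| 0.8 | 1.24 | 107% | 78.1% | 73.6% |

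**4. Chance imbalance between arms.** The difference in order share has expectation zero. Its variance is 2 × (0.25/30) × 150/149 = 0.0168, so its SD is 0.13. By simulation (200,000 draws) it is at least 0.20 in about 16% of trials and at least 0.33 in about 1.4%. At 0.20 the arm difference shifts by 0.4o, which is 0.12 SD for o = 0.3 and 0.20 SD for o = 0.5, against the 0.8 SD implied by f = 0.2.

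**5. Bias and type I error.** Trials were simulated with no arm effect, with order reversed at T2 and ignored in the analysis (8,000 per setting). The mean estimated arm difference was about 0. Type I error was 4.9% at both o = 0.3 and o = 0.5.

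**6. Chance imbalance at T1.** The number in one order within a group of 30 is hypergeometric (30 drawn from 150, of whom 75 have that order). Its SD is 2.46 and its 95% range 10 to 20. A split of 18:12 or worse occurs in about 31% of trials, and 20:10 or worse in about 6.5%. A T1 score carries ±o/2, so a T1 contrast between two groups shifts by o times the difference in their order shares. For 20:10 against 15:15 that is 0.167o, or 0.05-0.08 SD at o = 0.3-0.5.

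**7. Effect of modelling order.** With a constant position effect and T1 order in the change model, the residual variance returns to 0.60 for one degree of freedom. Power at N = 60 with 57 residual degrees of freedom is again 97.6%, provided order is close to balanced between arms.

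**The case against.** A reader might infer that order is unbalanced between groups or arms, and that this biases the BAT-MBT comparison. The article supports neither. It neither states nor excludes stratification of the list. Order comes from a randomised list and arm is randomised afterwards, so any arm imbalance is by chance. It has zero expectation and is already covered by the standard error. The added variance and the chance shift are also not two separate harms: the first is how the test accounts for the second.

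Further points stand against a larger claim:

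- The size of o is assumed, and at 0.1 SD the loss is negligible.
- Power at .05 stays above 90% with 60 patients over the assumed range. At .05/200 the same calculation gives 54% falling to 44-31%, but the low starting value there is a separate matter and should not be charged to block order.
- The reward and erotic tasks are untouched. So are the resting, sad mood and alcohol cue blocks, if the reversal at T2 concerns only the two counterbalanced blocks, which is the natural reading.
- An order term may be in an analysis plan that is not shown, and the article's analysis of (co)variance would admit one.

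The last point does not dispose of the matter. The article states the level of balance and the T2 rule outright. Those two rules together leave a position effect in each change score, and they do not protect the planned contrasts.

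**Conclusion.** The point holds as a matter of precision, not of bias. The stated rule does not ensure balance of block order within diagnostic group or therapy arm. With reversal at T2, a position effect enters each comorbid patient's change in the two therapy-matched blocks as +o or -o. Type I error is kept, and the expected shift in the arm contrast is zero.

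For an assumed o of 0.3-0.5 SD, the variance of change rises by 15-42%. Power at .05 falls from 98% to 96-91% with 60 patients, and from 96% to 93-88% with 54. The chance-imbalance figures also assume a single unstratified 75:75 list; a list already stratified or finely blocked would make them smaller. This is a minor point with a very cheap remedy.

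**What to change.** 1. Include T1 block order as a factor in the four-group T1 models and in the T1-T2 BAT-MBT models for the mindfulness and behavioral activation blocks. This is the essential part: it removes the added variance and adjusts for whatever imbalance occurs.
2. Stratify the existing order list by diagnostic group and, for comorbid patients, balance it 3:3 within each consecutive six. Since therapy groups are formed in sixes, balance by arm then largely follows although order is set before allocation.

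The cost is one model term and a stratified version of a list that the trial already generates. Balance of 3:3 alone would leave o² in the variance. It can also be lost when patients are excluded from the protocol or drop-outs are replaced, so step 2 supports step 1 and does not replace it.

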### Anatomical image

In order to assess the individual brain morphology of each participant, high-resolution T1-weighted anatomical images (MPRAGE) will be collected.

### Primary outcome

In this study, neural activation and connectivity in the reward system and default mode network are the primary outcome measures. Neural correlates of reward and emotion processing in patients and healthy controls will be assessed by means of fMRI. While the first measurement will identify common and/or distinct neural signatures underlying the comorbidity of alcohol dependence and depression, the second measurement allows investigating the influence of the psychotherapeutic interventions on these target brain mechanisms.

### Secondary outcome measures

Secondary outcome measures include craving and depression scores, as well as relapse rates.

### Predictors

Predictors include participants’ characteristics and personality traits as assessed by questionnaires (See Table 1), as well as ratings before, during and after scanning.

**Table 1 Tab1:** Schedule of measurements

Variable	Instrument	T0	T1	T2	T3
Neural activation and connectivity	fMRI assessment battery		⨯	⨯	
Demographic information	Interview/Self-report	⨯			
Psychopathology	Structured Clinical Interview for DSM-IV, Axis I,II	⨯			
Medication	Self-report		⨯		
Health Care resource utilisation	Interview/Self-report		⨯		
Alcohol Use	Form 90 Interview		⨯		⨯
Alcohol Dependence	Alcohol Dependence Scale		⨯	⨯	⨯
Craving	Obsessive Compulsive Drinking Scale Alcohol Urge Questionnaire		⨯	⨯	⨯
Depression	Beck Depression Inventar Montgomery and Asperg Depression Rating Scale		⨯	⨯	⨯
Rumination	Response-Styles-Questionnaire Perseverative Thinking Questionnaire		⨯	⨯	⨯
Mindfulness	Mindfulness Attention and Awareness Scale		⨯	⨯	⨯
Quality of life	Münchner Lebensqualitäts-Dimensionen Liste		⨯	⨯	⨯
Self-confidence	Rosenberg Selbstwert Skala Self-Acceptance Scale Forms of Self-Criticizing/Attacking and Self- Reassuring Scale		⨯	⨯	⨯
Smoking	Fargerstrom Test for Nicotine Dependence		⨯	⨯	⨯
Intervention Satisfaction	Self-report			⨯	

### Data analyses plan

Analyses will be conducted on an intention to treat and treatment completers principle.

### Behavioral data analyses

Analysis will be completed by using (repeated measures) analysis of variance (AN(C)OVA) in order to test group differences (AUD vs MD vs Co vs HC) and treatment groups (BAT vs MBT). Difference scores will be calculated. All measures will be compared between groups, as well as treatment groups and interaction effects will be explored. Wherever appropriate, missing data will be imputed using multiple imputation.

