### Sample size

Power calculations were conducted by means of the G*Power 3.1 software package [46]. According to pilot studies, an effect size of at least d = 1 can be assumed for the different paradigms and comparisons. For region of interest analysis with regions of 200 voxels, a sample of 30 per group should be sufficient to reach a power of 80% to detect differences at *p* < .05 (Bonferroni corrected for multiple tests). For the intervention study the same comorbid alcohol dependent and depressed participants will be randomly assigned to one of two group therapy interventions and asked to participate in a second fMRI session and follow up measurement. When assuming a small to medium effect size (*f* = .2) for the group x time interaction and a correlation among repeated measures of.7 (as typical for fMRI data), we achieve a power of 80% to detect differences at *p* < .05 (Boferroni corrected for a k = 200, region of interest) on the neural level even when we have to face a drop-out rate of 10%. While we expect an attrition rate of 20%, recruitment will be continued until the desired sample sizes are reached and drop-outs will be replaced by new participants.

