### Psychotherapeutic Interventions

Comorbid patients will be randomly assigned to one of two group therapies consisting of 6 participants. Both interventions consist of six sessions of 2 h therapy with 1 session per week offered by a psychotherapist. To increase adherence, ﻿each participant will receive an individual therapy session before the group therapy begins. The group therapy protocols in both arms are manualized and supervised by an experienced psychotherapist to ensure protocol adherence. Patients who missed more than one session or experienced a severe relapse during the intervention period will be excluded from the protocol. In the unexpected case of an adverse event or harm during the psychotherapeutic intervention (for example, severe aggravation like suicidality), the affected patient will also be excluded and additional in- or outpatient treatment will be offered by the psychotherapist.

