One limitation of the study might concern the lack of a proper control group for the investigation of the treatment effects (for example waiting control group). However, this study was not designed to evaluate treatment effects per se but rather to investigate the neurobiological correlates of established psychotherapeutic interventions. With this, we are specifically interested if the targeted interventions positively alter the pathophysiology of comorbid patients and whether this is restricted to patients with a specific neurobiological signature. A second challenge affects the recruitment of comorbid depressed and alcohol dependent patients. Not only for the fMRI measurement, but also for the feasibility of the group therapy patients abstinence is a prerequisite. In order to motivate comorbid patients to participate in the group therapy and to stay abstinent, we want to guarantee a fast study enrolment, as well as ensure a short latency between study enrolment and begin of group therapy. For that reason, we decided for a group randomization of 6 participants per block. With this, we might risk recruitment-dependent biases. However, due to many different recruitment strategies and sources, we hope to reduce this potential bias to a minimum.

To reach the project results is one of the key issues and core challenges to contribute to a better neurobiological understanding and treatment of comorbid depression and alcohol dependence. The project will help to improve knowledge on pathophysiology, identify targets for treatment development, detect subgroups for treatment selection, and facilitate the use of neurobiology findings in the understanding of comorbid alcohol dependence and depression.

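### BAT and MBT are delivered in therapy groups of six, but the stated tests and power calculation treat patients as independent, so BAT-MBT standard errors are too small if outcomes correlate within groups

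*Protocol article*

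**What the plan says.** - **Delivery** (Psychotherapeutic Interventions): "Comorbid patients will be randomly assigned to one of two group therapies consisting of 6 participants". Each group meets for six weekly two-hour sessions.
- **Allocation** (Randomization): "the randomization order will be determined with a block randomization with 6 participants per block for each treatment arm". The Discussion goes further: "we decided for a group randomization of 6 participants per block". It names recruitment-dependent bias as the risk of this scheme and does not mention correlation within groups.
- **Numbers** (Participants): "Sixty comorbid alcohol dependent and depressed patients, 30 alcohol dependent only and 30 depressed only patients will be included for T1 assessment".
- **Analysis** (Behavioral data analyses): "Analysis will be completed by using (repeated measures) analysis of variance (AN(C)OVA) in order to test group differences". BAT against MBT is listed among the comparisons, and difference scores are to be calculated. Therapy group is not in the model.
- **Power** (Sample size): "When assuming a small to medium effect size (*f* = .2) for the group x time interaction", with a correlation of .7 between repeated measures, the article claims 80% power at p < .05, Bonferroni-corrected for k = 200, even with 10% drop-out. No ICC or design effect enters.

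**The concern.** Patients who sit through the same sessions with the same peers may end up more alike than patients from different groups. An individual-level AN(C)OVA counts each of them as an independent observation. If whole sixes are allocated together, as the Discussion indicates, the group is also the unit of randomisation. If patients are instead randomised one by one, shared treatment can still produce correlation after baseline in both arms.

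At stake is the only randomised comparison in the study. With about five groups per arm, one or two unusual groups could be reported as a difference between therapies.

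**Working it through.** **Inputs.** From the article: 60 randomised patients, groups of 6, f = .2, correlation .7, two time points, 10% drop-out. Derived: 60/6 = 10 groups, 5 per arm; 60 × 0.9 = 54 analysed, or 54/10 = 5.4 per group. Assumed: the ICC, 0 to .20. Since difference scores are planned, the relevant ICC is that of the change from T1 to T2.

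**Step 1: the article's own power figure.** For a within-between interaction with two groups and two time points, λ = f² × N × 2/(1 − ρ), with 1 and N − 2 degrees of freedom. For N = 54, λ = 0.04 × 54 × 2/0.3 = 14.4. Power is 96.1% at alpha .05 and 45.6% at alpha .05/200 = .00025. The stated 80% matches neither. That mismatch is a separate issue; 96% at alpha .05 is the reference point under independence.

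**Step 2: loss of precision.** The design effect is 1 + (6 − 1) × ICC. The true standard error is its square root times the one that the individual-level test reports, and the effective sample is 60 divided by it.

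**Step 3: type I error.** 40,000 trials per ICC were simulated with 5 groups of 6 in each arm and no true difference. Each was tested at a two-sided 5% by an individual-level test (58 df, critical t 2.00) and by a test on group means (8 df, critical t 2.31).

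| ICC | Design effect | SE factor | Effective N | Type I error, individual-level | Type I error, group-level |
|---|---|---|---|---|---|
| 0 | 1.00 | 1.00 | 60 | 5.0% | 4.8% |
| .01 | 1.05 | 1.02 | 57 | 5.5% | 5.1% |
| .05 | 1.25 | 1.12 | 48 | 8.1% | 5.1% |
| .10 | 1.50 | 1.22 | 40 | 11.0% | 4.9% |
| .20 | 2.00 | 1.41 | 30 | 17.1% | 4.8% |

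**Step 4: interaction power with clustering.** At alpha .05 with N = 54, divide λ = 14.4 by 1 + (5.4 − 1) × ICC and use 8 denominator df.

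| ICC | Divisor | λ | Power |
|---|---|---|---|
| 0 | 1.000 | 14.4 | 91% |
| .01 | 1.044 | 13.8 | 90% |
| .05 | 1.220 | 11.8 | 85% |
| .10 | 1.440 | 10.0 | 79% |
| .20 | 1.880 | 7.7 | 68% |

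The fall from 96% to 91% at ICC 0 comes from the smaller degrees of freedom alone.

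**The case against.** **The harm is conditional.** A reader might infer that the BAT-MBT p-values are certainly too small. The article gives no ICC, so it does not support that. At ICC 0 the individual-level test is correct, and at .01 the error is 5.5%. This stands; the inflation becomes material from about .05.

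**The primary outcome is neural.** The AN(C)OVA is stated for behavioural data. For fMRI activation the article describes only the first-level model, and a condensed article may leave the second level to a fuller plan. It would go too far to say that the imaging contrasts are shown to ignore therapy group. The link to the neural outcome is the Sample size section, which computes neural-level interaction power without an ICC.

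**Treatment effects are not the main aim.** The Discussion says that the study was not designed to evaluate treatment effects per se, and the primary aim concerns neurobiological mechanisms. This lowers the weight of the point but does not remove it: the article calls the study a randomised controlled trial, powers the interaction, and includes the second scan in its primary outcome.

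**Ten groups and 8 df are approximate.** Drop-outs are to be replaced and 20% attrition is expected. Reaching 60 completers would take 60/0.8 = 75 patients, roughly 12 groups and 10 df. The Randomization section alone could also be read as ordinary blocked randomisation of individuals. Neither point rescues the independence assumption, because group delivery is certain.

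**Low power after Bonferroni correction.** With clustering, power at .05/200 is about 7% at ICC .05 and 5% at .10, and a reader might blame clustering. Most of the shortfall is there without it: power is 46% with independent patients and 11% with 8 df at ICC 0.

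**Therapist effects.** A reader might infer that therapist is confounded with arm. The article says only that a psychotherapist offers the sessions, not how therapists map to groups or arms.

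**Conclusion.** The concern holds in conditional form. Treatment is delivered in groups of six, yet the stated BAT-MBT tests and the interaction power calculation treat patients as independent. If outcomes correlate within therapy groups, the standard errors are too small by a factor of 1.02 to 1.41 for ICCs from .01 to .20, and type I error at a nominal 5% rises to between about 5.5 and 17%. These figures assume about five equal groups of six per arm and an ICC that the article does not give. Only BAT-MBT comparisons at T2 and follow-up are affected; the T1 four-group comparison precedes group therapy and is untouched. At alpha .05 the trial would keep reasonable interaction power under a correct analysis unless the ICC is large.

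**What to change.** - **Continuous outcomes, including region-of-interest means:** compare BAT with MBT on T1-T2 change, or on T2/T3 values adjusted for baseline, in a linear mixed model with a random effect for therapy group and small-sample degrees of freedom (Kenward-Roger or Satterthwaite). A group-level test of arm against therapy-group-within-arm is an alternative; the two need not agree exactly when group sizes differ.
- **Relapse:** use a logistic mixed model or compare group-level proportions, because the linear-model corrections do not apply to a binary outcome.
- **Power:** restate the interaction power over a range of ICCs, as in the second table. Treat the k = 200 correction as a separate matter.
- **Allocation:** say plainly whether whole groups or individuals are randomised, so that Randomization and Discussion agree.

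This changes analysis wording only, since group membership is known from delivery. The cost is wider intervals and a lower stated power, including a small loss of power even if the ICC proves to be zero. The error term should be fixed before BAT-MBT results are seen.
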